### Analysis Strategy

Physical activity data, clinical data, and HRQL measures will be analyzed using Linear-mixed model (LMM) analyses employing intention-to-treat principles [40] using the Statistical Program for Social Sciences (SPSS) 16. LMM analyses examine changes from baseline to each follow-up time point for each intervention group compared to the changes for the same time period for the control group [41] (See Appendix A).

LLMs use all available data and provide a valid analysis when data are missing at random. Tests will be conducted to examine if missing data are missing at random. Suitable multiple imputation methods will be utilized if the data are found to be not missing at random. A total of three planned comparisons will be completed and include: Group 1 **to **Group 2, Group 1 **to **Group 3, and Group 2 **to **Group 3. The alpha levels will be reported along with effect sizes (following Cohen's guidelines) for each of the analyses [42].

Prior to analyses, any baseline differences between groups for variables (based on the literature) that may be associated with activity levels of participants will be assessed for baseline balance. These include, age, gender, level of education, income, marital/partner status, diabetes duration, BMI, medication (i.e., insulin), physical disability index, and A1C levels. Depending on the variables (categorical or continuous measures) chi-square tests or one-way ANOVAs will be conducted to assess baseline balance on the above-mentioned variables. Given the inconsistency of these variables in their association of PA in this population [10] the primary analyses will only co-vary for baseline physical activity. However, we will also present adjusted results, controlling for any of these variables displaying significant differences (p < .05) between groups at baseline.

We will compare study dropouts with individuals who completed the study on physical activity levels, demographic and medical variables. We also plan to compare drop-out rates between the different study groups.

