**Method/Design:**

Participants (N = 287) were randomly assigned to one of three groups consisting of the following intervention strategies: (1) standard printed PA educational materials provided by the Canadian Diabetes Association [i.e., Group 1/control group)]; (2) standard printed PA educational materials as in Group 1, pedometers, a log book and printed PA information matched to individuals' PA stage of readiness provided every 3 months (i.e., Group 2); and (3) PA telephone counseling protocol matched to PA stage of readiness and tailored to personal characteristics, in addition to the materials provided in Groups 1 and 2 (i.e., Group 3). PA behaviour measured by the Godin Leisure Time Exercise Questionnaire and related social-cognitive measures were assessed at baseline, 3, 6, 9, 12 and 18-months (i.e., 6-month follow-up). Clinical (biomarkers) and health-related quality of life assessments were conducted at baseline, 12-months, and 18-months. Linear Mixed Model (LMM) analyses will be used to examine time-dependent changes from baseline across study time points for Groups 2 and 3 relative to Group 1.

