### Primary outcomes

*Physical activity behaviour *was assessed by subjective and objective methods. Self-reported physical activity was collected using a slightly modified version [10] of the validated Godin Leisure-Time Exercise Questionnaire [28] that asked participants to report the average number of times per week and average duration, in the past month, they engaged in vigorous (rapid heart beats, sweating), moderate (not exhausting, light perspiration) and mild (minimal effort and no perspiration) intensity physical activity for a minimum of 10 minutes per session. Participation responses for the vigorous and moderate activity categories were then added to obtain summary scores of weekly PA and include weighted and non-weighted scores for PA intensity (i.e., weekly moderate intensity minutes multiplied by 4 Metabolic equivalents and vigorous intensity multiplied by 7.5 Metabolic equivalents) [29]. Mild intensity activity responses were not included in the calculation since this level of intensity has no proven association with health benefits and is not included in the current practice guidelines.

As an objective measure of PA, total daily steps were collected with a pedometer over 3 days. Participants were instructed to wear a pedometer during waking hours and to record the total daily step counts in a log.

The study's second primary outcome, glycosylated hemoglobin (A1C), was measured using a turbidimetric immunoinhibition method on a Synchron LX20 analyser (Beckman Coulter, Fullerton CA) [30].

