### Statistical power and sample size

The study's primary analysis is the comparison of physical activity behaviour between the three study groups, from baseline to the 12-month time-point. Assuming a moderate correlation (r = 0.5) between baseline and post-intervention, to detect a mean difference of 0.5 standard deviation between study groups for the main dependent outcome (i.e., physical activity behaviour) at post-intervention (as suggested by Cohen) [43] the required sample size is 76 participants per group (power = 0.80; alpha = 0.01 [44]. Secondary analyses will examine the PA behaviour change between the study groups across the other study time-points (i.e., 6 and 18 months).

The sample size is also adequate to assess differences between the groups on the study's secondary outcomes of the psychosocial measures and nutrition behaviours, [43] and based on published intervention studies to date, it is more than adequate (power >0. 80; alpha = 0.05) to independently detect differences on the anthropometric and biometric outcomes (i.e., body weight, hip-waist ratio, fitness measures, A1C, fasting glucose, fasting lipid profile, plasma insulin levels, and C-reactive protein).

Anticipating a maximum study drop-out rate of 20% at 12-months (study's primary end-point), and 30% at 18-months we enrolled 287 individuals. The dropout rate was based on conservative estimates from other similar type of investigations on individuals with type 2 diabetes [45] and our study's retention strategies.

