## Appendix A

LMM model statement is: yij = ÿ0 + ÿ1.tij + ÿ2.gi1+ ÿ3.gi2 + ÿ4.(gi1*tij) + ÿ5.(gi2*tij)+bi0 + bi1 * tij + ÿij, i = 1, ..., 287; j = 1, ..., 6, where ÿ's are the fixed effects coefficients, b's are the random effects coefficients, the product terms gij*tij are interaction terms of group-by-time, and ÿij is the error for observation j in group i. The command (in SPSS) used will be as follows [one group factor (GROUP) and one repeated measures factor (TIME), where ACTIVITY (and other outcomes) is the dependent variable and ID is the subject variable].

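### For A1C, biomarkers and HRQL the planned mixed model is not valid under drop-out that depends on recorded 3- to 9-month activity, and the imputation rule would not catch it; the likely bias is small

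*Protocol article*

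**What the plan says.** The abstract gives two schedules. For self-reported activity and its psychological correlates, "related social-cognitive measures were assessed at baseline, 3, 6, 9, 12 and 18-months". For the laboratory and quality-of-life outcomes, "Clinical (biomarkers) and health-related quality of life assessments were conducted at baseline, 12-months, and 18-months". A1C is not a minor endpoint: under Primary outcomes the protocol says the study's "second primary outcome, glycosylated hemoglobin (A1C), was measured using a turbidimetric immunoinhibition method".

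All of these outcomes go through one type of model: "Physical activity data, clinical data, and HRQL measures will be analyzed using Linear-mixed model (LMM) analyses employing intention-to-treat principles". Appendix A writes it out with group, time and group-by-time as fixed effects and one outcome at a time, "where ACTIVITY (and other outcomes) is the dependent variable and ID is the subject variable". The Analysis Strategy adds baseline activity as the only covariate in the primary analyses.

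On missing data the same section says "LLMs use all available data and provide a valid analysis when data are missing at random" (the abbreviation evidently means the linear mixed models). It plans tests of whether data are missing at random, and multiple imputation if they turn out not to be. It names no imputation variables. Drop-outs and completers are to be compared on activity and other variables, and drop-out rates between arms, but neither comparison is said to feed into the outcome models.

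On attrition, the sample size section reads "Anticipating a maximum study drop-out rate of 20% at 12-months", with 30% expected at 18 months.

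**The concern.** A likelihood-based mixed model is valid under missing at random given the data inside that model. The activity model contains the 3-, 6- and 9-month values, so drop-out that follows a poor early response is accounted for. The A1C, biomarker and HRQL models do not contain them. If people whose activity fails to rise are more likely to leave, and activity is related to A1C, those who stay differ from those who left in a way that the A1C model cannot see, although the trial has recorded it.

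The stated safeguard works the wrong way round here. Drop-out explained by recorded activity is missing at random given everything collected, so a rule that starts imputation only when data are judged not missing at random leaves the interim scores out. This does not depend on whether such a judgement can be made from observed data.

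At stake are the 12- and 18-month contrasts for a named primary outcome and for the biomarkers and HRQL.

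**Working it through.** **1. What each model sees for someone lost between month 9 and month 12**

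| Outcome | Own values in the model | Activity in the model |
|---|---|---|
| Activity (Godin) | 0, 3, 6, 9 months | the same values |
| A1C, biomarkers, HRQL | baseline only | baseline only, as covariate |

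**2. The plan's attrition figure.** 76 per group × 3 = 228, and 228 / 0.8 = 285, against 287 enrolled. The 20% loss is therefore the plan's own and leaves 287 × 0.8 / 3 = 76.5 per arm at 12 months.

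**3. Yardstick.** The standard error of a two-arm 12-month contrast, adjusted for baseline, is √(2(1 − r²)/n) in outcome SD. With n = 76:
- r = 0.5 (the plan's value for activity): √(1.5/76) = 0.140
- r = 0.6 (assumed): √(1.28/76) = 0.130

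**4. Simulation of the A1C contrast, large samples per arm**

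*From the protocol:* 20% loss, activity effect 0.5 SD, baseline-to-follow-up correlation 0.5 (stated for activity, borrowed for A1C).

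*Assumed, not in the protocol:* correlation ρ of interim activity with 12-month A1C from -0.2 to -0.4; correlation of baseline with interim activity 0.5 to 0.7; the drop-out rules below.

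*Model:* A1C at 12 months = 0.5 × baseline + 0.866 × (ρ × activity + noise). The true contrast is 0.866 × ρ × 0.5, that is -0.087, -0.130 and -0.173 SD at ρ = -0.2, -0.3 and -0.4.

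*Estimate:* regress on the stated predictors among those retained, then average the predictions over everyone randomised.

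| Drop-out rule (20% loss per arm) | Baseline A1C + baseline activity (as planned) | Interim activity added |
|---|---|---|
| Same dependence in both arms | no bias | no bias |
| Control 37% vs 5% at -1/+1 SD of activity; Group 3 26% vs 14% | shrinks 13–19% (0.01–0.03 SD) | no bias |
| Dependence in control only | shrinks 21–32% (0.02–0.05 SD) | no bias |

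The log-odds slopes in the second row are (logit 0.05 − logit 0.37)/2 = (−2.94 + 0.53)/2 = −1.2 per SD in control and (logit 0.14 − logit 0.26)/2 = (−1.82 + 1.05)/2 = −0.4 in Group 3. No bias means zero within simulation error. If baseline activity is left out, as in the Appendix A formula read literally, the last two rows become 23–25% and 39–41%.

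**5. How far the result moves under other assumptions.** A second simulation used a baseline-to-12-month outcome correlation of 0.6, activity–outcome correlations of -0.1 to -0.4 and drop-out slopes of 0.7 to 1.5 in size.
- Same slope and same overall rate: zero bias.
- One common drop-out rule, with the activity effect itself pulling the rates apart (for example 24.5% vs 15.5%): 0.00–0.03 SD.
- Dependence in the intervention arm only: 0.00–0.08 SD at 20% loss and 0.01–0.11 SD if that arm loses 30%. Here the benefit is exaggerated, so the direction depends on which arm carries the dependence.
- Dependence in opposite directions in the two arms, steep slopes: up to 0.15 SD.
- Interim activity included: zero within simulation error throughout.

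**The case against.** The strongest reply is that the quoted sentence is the standard statement about mixed models, that auxiliary and imputation variables are usually chosen in the analysis plan, and that a journal article need not list them. The promise of suitable imputation does not exclude interim activity. This stands as far as an unnamed variable list goes. It does not cover the trigger, which the article does fix: as written, the situation in which interim activity helps most is the one in which imputation is not called for.

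Second, it would be wrong to say that the interim activity data go unused or that a lost participant contributes a baseline A1C alone. Drop-outs and completers are compared on activity, and baseline activity is a covariate. Both corrections stand. The covariate lowers the shrinkage in the second scenario from about 24% to 13–19%.

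Third, a reader might infer that the A1C result will be biased because only Group 3 receives counselling calls. The documents do not support that. They give no information on how drop-out depends on activity in any arm, and all participants get reminder calls, repeat contact attempts, re-sent questionnaires and a final letter. Differential dependence is possible but assumed.

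Fourth, a reader might extend the point to the trial's main result. That does not follow: the sample size section defines the primary analysis as activity from baseline to 12 months, and that model contains the interim values.

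**Conclusion.** The point holds in a limited form. For outcomes measured at 0, 12 and 18 months, the claim of using all available data and being valid under missing at random applies only to drop-out explained by the outcome's own values and baseline activity. It does not extend to drop-out that depends on recorded 3- to 9-month activity, and the imputation rule does not close that gap.

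The size is modest. Two conditions are needed: interim activity must be related to the outcome, and drop-out must act differently by arm. Under the assumptions of step 4 the A1C contrast shrinks by about 13–32%, or 0.01–0.05 SD. Against the standard error, 0.05/0.13 is about 0.4 at most. The percentages look large because the assumed A1C effect is itself small (0.09–0.17 SD). The larger figures in step 5 need steeper slopes, heavier loss or opposite drop-out patterns, none of which the protocol suggests. Only the 12-month A1C contrast was simulated; the reasoning for biomarkers, HRQL and month 18 is the same, but their size was not computed. This is a low-cost improvement, not a flaw that threatens the trial.

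**What to change.** Keep the planned mixed model as the main estimate. Beside it, and whatever any missingness test shows, pre-specify a multiple imputation under missing at random, run separately by arm, for the 12- and 18-month A1C, biomarker and HRQL contrasts. Include the outcome's own baseline and the Godin scores at baseline, 3, 6, 9 and 12 months as auxiliary variables. The month-12 score is useful because questionnaires and blood results are logged separately, so activity may be known where A1C is missing.

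Reword the sentence on available data so that it refers to the data in each outcome's own model.

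The cost is extra analysis work and a second estimate to report for each of these outcomes. No new data or change in procedure is needed. Replacing the mixed model by the imputation estimate is not recommended on this evidence, because it trades one set of modelling choices for another.

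### The missing-data rule depends on a test of missing at random that observed data cannot provide, so the choice of analysis should not rest on it

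*Protocol article*

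**What the plan says.** The protocol article's Analysis Strategy section sets out the handling of missing data in three consecutive statements:

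- The model's assumption: "LLMs use all available data and provide a valid analysis when data are missing at random" (the abbreviation is a misprint for LMM).
- The trigger: "Tests will be conducted to examine if missing data are missing at random".
- The consequence: "Suitable multiple imputation methods will be utilized if the data are found to be not missing at random".

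The same section adds two descriptive checks: "We will compare study dropouts with individuals who completed the study on physical activity levels, demographic and medical variables", and "We also plan to compare drop-out rates between the different study groups". It also says that the primary analyses adjust for baseline physical activity only, and it plans three pairwise group comparisons. Appendix A gives the model as group, time, their interactions, and a random intercept and slope.

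The section on statistical power and sample size gives the expected loss: "Anticipating a maximum study drop-out rate of 20% at 12-months (study's primary end-point), and 30% at 18-months we enrolled 287 individuals".

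**The concern.** The rule makes the analysis depend on a finding that the data cannot deliver. MAR means that, given what has been observed, missingness does not depend on the values that were not observed. MNAR means that it does. The two differ only in the part of the data that is absent, so no test on the observed part can separate them. A fuller plan could name a test, but it could not make this trigger work.

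Two errors can follow. A significant result may be taken as proof of MNAR when it shows only dependence on measured variables. A non-significant result may be taken as confirmation of MAR, closing the question without evidence.

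This matters here because the expected loss is not small. Participants are told their group by telephone, and one primary outcome is self-reported activity collected by mailed questionnaire. It is plausible, though the documents do not show it, that people who have become less active are less likely to reply, and that this differs between a leaflet arm and a counselled arm.

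**Working it through.** **1. The plan's own figure.** The sample-size section requires 76 per group and allows 20% dropout at 12 months: 76 / (1 − 0.20) = 95 per group, and 95 × 3 = 285, against 287 enrolled. The dropout allowance therefore reproduces to within two participants. On 287, the stated maxima mean about 0.20 × 287 = 57 people without 12-month data and 0.30 × 287 = 86 without 18-month data.

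**2. What the tests can show.** Suppose the dropouts in an arm have a mean that differs from the MAR prediction by an amount δ. The observed records are the same whatever δ is, so they carry no information on it. Tests for missing completely at random, and the planned comparison of dropouts with completers, use observed variables only. They can detect dependence on those variables and nothing more.

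**3. The rule under each possible state.**

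| State | What a test can show | LMM under MAR | What imputation adds |
|---|---|---|---|
| Missingness depends on variables in the model | May reject | Valid, by the plan's own statement | Nothing, if it uses the same variables |
| Missingness depends on measured variables outside the model (for example education, BMI, social-cognitive scores) | May reject | Can be biased | Can help, if those variables enter the imputation |
| MNAR | Cannot be identified as such | Biased | Repairs nothing without an explicit MNAR assumption |

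The condition written into the rule is the third row. The tests speak only to the first two.

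**4. Size, on assumed values.** Let p be the dropout proportion in an arm and δ the shortfall of its dropouts below the MAR prediction, in SD units. The MAR analysis overstates that arm's mean by p × δ. For arm A minus arm B:

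bias = p_A δ_A − p_B δ_B

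With one arm affected (p from the plan, δ assumed):

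| | δ = 0.25 | δ = 0.5 |
|---|---|---|
| p = 0.20 (12 months) | 0.20 × 0.25 = 0.05 | 0.20 × 0.5 = 0.10 |
| p = 0.30 (18 months) | 0.30 × 0.25 = 0.075 | 0.30 × 0.5 = 0.15 |

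Against the 0.5 SD target difference, the 12-month values are 0.05 / 0.5 = 10% and 0.10 / 0.5 = 20%. If only the comparator arm is affected the sign reverses. If both arms have equal p and δ, the bias cancels.

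**5. Does ordinary imputation remove it?** This was simulated with two arms, 400,000 subjects, a true difference of 0.50 SD, a baseline correlation of 0.5 (the plan's value) and dropout of 18% to 24% per arm. A baseline-adjusted regression on the observed data stood in for the LMM. It was compared with MAR-based multiple imputation using the same variables.

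| Assumed mechanism | Regression on observed data | MAR-based imputation |
|---|---|---|
| MAR (depends on baseline) | 0.498 | 0.498 |
| MNAR in both arms | 0.469 | 0.469 |
| MNAR in the intervention arm only | 0.647 | 0.648 |

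The two methods agree within 0.001 SD throughout, so imputation on the same variables removes none of the MNAR bias. The direction differs: about 0.03 SD too low with both arms affected, and about 0.15 SD too high with one. The last mechanism is a strong one. With 22.1% dropout in that arm it corresponds to δ of about 0.147 / 0.221 = 0.67 SD, above the range in step 4. No auxiliary variables were simulated, so the result says nothing against the second row of the table in step 3.

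**The case against.** The best defence is that the wording is loose but the intention is workable. The authors may mean that they will look for predictors of dropout and, if these lie outside the model, impute with them. That is sound practice. The model holds only group, time and baseline activity, dropout may well depend on other measured variables, and the dropout-versus-completer comparison would reveal it. This stands, and it is why imputation keeps a supporting role in the fix. It does not rescue the rule as written, which is conditional on finding MNAR.

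Several stronger readings are tempting, and the documents do not support them:

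- *That the plan commits to standard imputation and so repeats the assumption it sets out to repair.* The text says suitable methods. Imputation can be built under MNAR, and a fuller plan might specify it.
- *That a test result replaces the primary analysis.* The article says imputation will be used. It does not say that it displaces the LMM, and it could be supplementary or feed the same model.
- *That the trial has no MNAR sensitivity analysis.* The article states none, but a condensed article commonly leaves such detail to a plan that is not shown.
- *That the effect will be inflated by 10% to 20% of the target.* No δ comes from the documents, the 20% and 30% are stated maxima, and the direction depends on which arms are affected.

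The retention procedures and the comparison of dropout rates are relevant to the risk of MNAR. They do not test for it.

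**Conclusion.** The point holds in this form. The article fixes a rule whose condition observed data cannot establish. What the tests can find, dependence on measured variables, leaves the LMM valid when those variables are in the model and calls for auxiliary-variable imputation when they are not. What the rule names, MNAR, cannot be found, and imputation under the usual MAR assumption would not correct it.

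That conclusion rests on logic and needs no figure. The size is illustrative: 0.05 to 0.10 SD at 20% dropout and 0.075 to 0.15 SD at 30%, assuming δ of 0.25 to 0.5 SD in one arm only. It is not a prediction of bias in this trial.

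**What to change.** - Delete the test of MAR and the trigger attached to it.
- Keep the LMM under MAR, on all randomised participants, as the primary analysis.
- Keep the dropout comparisons as description. Where dropout is related to measured variables outside the model, add multiple imputation that includes those variables as a supporting analysis.
- Regardless of any test, run a pre-specified MNAR sensitivity analysis for all three 12-month contrasts: delta-adjusted multiple imputation over a stated range, with the tipping point reported. Let the deltas differ by arm and include Group 1. One common delta applied to Groups 2 and 3 would barely move the Group 2 to Group 3 contrast at similar dropout rates, and it would leave Group 1 dropouts untested.

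The cost is a change of wording and a modest amount of extra analysis. No new data are needed.

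### A1C, biomarkers and HRQL are compared as change from baseline without covariate adjustment for each outcome's own baseline, which gives away some precision on the second primary outcome

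*Protocol article*

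**What the plan says.** The Primary outcomes section names A1C alongside PA: "The study's second primary outcome, glycosylated hemoglobin (A1C), was measured". The abstract gives its visits: "Clinical (biomarkers) and health-related quality of life assessments were conducted at baseline, 12-months, and 18-months".

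The Analysis Strategy assigns PA, clinical and HRQL measures to the same linear mixed model (LMM) and describes the contrast: "LMM analyses examine changes from baseline to each follow-up time point for each intervention group", set against the control group's change over the same period. On covariates it says that "the primary analyses will only co-vary for baseline physical activity". The reason given is that the listed baseline variables relate inconsistently to PA. A1C is on that list. It enters only an additional set of adjusted results, and only if the groups differ on it at p < .05.

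Appendix A writes out one model with group, time and group-by-time terms, a random intercept and a random slope. Baseline is one of the repeated occasions and there is no baseline covariate. The appendix extends the model beyond PA: "where ACTIVITY (and other outcomes) is the dependent variable and ID is the subject variable".

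**The concern.** For the PA outcomes, baseline PA is the outcome's own starting value. For A1C, glucose, lipids, C-reactive protein, SF-12 and EQ-5D it is the baseline of a different variable. The covariate one would want in an A1C model is baseline A1C. The trial collects it, but the plan uses it as a covariate only if a significance test happens to flag it.

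The covariate sentence can be read in two ways. If it governs all primary outcomes, the A1C model adjusts for baseline PA. If it governs PA only, the article names no standing covariate for A1C. On either reading the A1C contrast is a difference in change, with no regression on baseline A1C. The reason given for keeping covariates few concerns associations with PA and does not bear on an outcome's own baseline.

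What is at stake is precision on a declared primary outcome, and on the biomarkers and HRQL scores analysed the same way.

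**Working it through.** **Inputs from the protocol (Statistical power and sample size).** For PA: "Assuming a moderate correlation (r = 0.5) between baseline and post-intervention", "to detect a mean difference of 0.5 standard deviation between study groups", and "the required sample size is 76 participants per group (power = 0.80; alpha = 0.01"). For A1C and the other biometric outcomes the section claims power above 0.80 at alpha 0.05, but gives no effect size, SD or correlation.

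**The plan's own figure.** n per group = 2v(z₁₋α/₂ + z₀.₈)²/d², where v is the variance factor in units of SD². With d = 0.5 and two-sided alpha 0.01:
- v = 1 - 0.5² = 0.75 (own baseline as covariate): n = 71.
- v = 2(1 - 0.5) = 1.00 (change score): n = 94.

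Neither gives 76. The enrolment step does follow: 76/(1 - 0.20) = 95, and 3 × 95 = 285, against 287 enrolled. The mismatch on 76 is a separate matter; here 76 serves only as the number analysed per group at 12 months.

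**Variance of the 12-month contrast.** Assume equal variances, correlation r between visits, and visits at 0, 12 and 18 months.
- Free baseline group means and unrestricted visit means: v = 2(1-r), the change-score value.
- Own baseline as covariate, or baseline means constrained equal: v = 1-r².

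Generalised least squares for the three visits confirms both:

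| r | Free baseline means | Own-baseline adjusted |
|---|---|---|
| 0.5 | 1.00 | 0.75 |
| 0.6 | 0.80 | 0.64 |
| 0.7 | 0.60 | 0.51 |
| 0.8 | 0.40 | 0.36 |

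**Power.** Assumptions: 76 per group, two-sided alpha 0.05, normal approximation, effect d / √(2v/76). The values of r and d for A1C are assumed.

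| r | 0.4 SD: change → adjusted | Gain | 0.5 SD: change → adjusted | Gain |
|---|---|---|---|---|
| 0.5 | 69.4% → 81.3% | 11.9 | 86.9% → 94.5% | 7.6 |
| 0.6 | 78.7% → 86.9% | 8.2 | 93.1% → 97.1% | 3.9 |
| 0.7 | 88.9% → 93.2% | 4.3 | 97.8% → 99.1% | 1.2 |
| 0.8 | 97.4% → 98.4% | 1.0 | 99.8% → 99.9% | 0.1 |

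At 0.3 SD the gains are 11.4, 9.5, 7.0 and 3.7 points.

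**Time as written in Appendix A.** The equation carries time as a single linear term. Under compound symmetry, ignoring the random slope, the 12-month contrast has v = 0.43 with free baseline means and 0.30 with constrained means at r = 0.5, and 0.26 against 0.21 at r = 0.7. The power table does not carry over to that model, but the loss of precision remains.

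**Does baseline PA help?** A simulation of 4000 replicates (76 per group, r = 0.5, 0.5 SD, assumed PA-A1C correlation of -0.2) gave power of 0.872 for change alone, 0.866 for change with baseline PA and 0.934 for own-baseline adjustment. Baseline PA added nothing.

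**Chance imbalance.** A chance baseline difference D shifts the change contrast by (1-r)D: for D = 0.2 SD, by 0.10 SD at r = 0.5 and 0.06 SD at r = 0.7. Since 2(1-r) = (1-r²) + (1-r)², this shift is the second term, already counted in the variance. At r = 0.5: 1.00 = 0.75 + 0.25.

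**The case against.** The strongest reply has four parts.

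1. *Own baseline is already in the model.* A reader might infer from the covariate sentence that A1C is analysed without regard to its baseline. The documents do not support that. The contrast is a change from each outcome's own baseline, and baseline is one of the repeated occasions. This stands; the remaining point is subtraction against adjustment.

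2. *The covariate sentence is about PA.* The list before it and the reason given both concern PA, and the sample-size section defines the primary analysis as PA. That is the more natural reading, but the wording says primary analyses while A1C is a declared primary outcome. On this reading too, the stated model for A1C makes no own-baseline adjustment.

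3. *A condensed article leaves such detail to the analysis plan.* Appendix A omits even baseline PA, so it is not a full covariate list, and the SPSS command it announces is not in the text at hand. This tempers the point. Even so, the article does fix the contrast, the covariate rule and the condition on which baseline A1C enters, so more than missing detail is at issue.

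4. *The size is unknown.* A reader might take 8 to 12 power points as this trial's loss. The documents do not support that: r = 0.5 is stated for PA only, and no effect size is given for A1C. This also stands.

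Nor do the documents support a claim of bias. Randomisation makes the change contrast unbiased, and the chance-imbalance shift is part of the variance loss, not a further harm.

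**Conclusion.** The point holds as a matter of efficiency, not validity. As stated, the plan subtracts the own baseline of A1C, the biomarkers and HRQL but does not adjust for it as a covariate, whichever way the covariate sentence is read. Adjustment would cut the contrast's variance by 25% at r = 0.5 (1.00 to 0.75) and by 15% at r = 0.7 (0.60 to 0.51), with unrestricted visit means.

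The gain in power depends on a correlation and an effect size that the protocol does not give for A1C. It is worthwhile if r is near 0.5 to 0.6 and close to nil at r = 0.8 for effects of 0.4 to 0.5 SD. No case computed showed a loss. Because a declared primary outcome is affected and the remedy is cheap, the change is worth making.

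**What to change.** State that the baseline-PA covariate sentence applies to the PA outcomes. Then add that the primary analysis of every other outcome adjusts for that outcome's own baseline, regardless of any balance test. For the A1C model, take A1C off the list of variables that enter only if p < .05.

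The preferred form keeps baseline as a response and constrains its mean to be equal across the three groups. This retains participants whose baseline is missing, which matters because the Recruitment and Randomization section describes lists of people whose blood data had not yet arrived. The alternative is to model the 12- and 18-month values with own baseline, by time, as covariate; without imputation, that drops anyone lacking a baseline.

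The cost is a changed model statement and, in the covariate form, one or two degrees of freedom (two when baseline interacts with the two follow-up visits). No new data or participants are needed.
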